### Reminder intervention

In the group receiving both SMS and phone calls (Group 4), the SMS reminder, in French or in English, will be sent between 08:00 and 12:00 AM, 72 hours before the appointment followed by a reminder phone call 48 hours before the appointment. The SMS will be sent manually. The SMS will serve as an appointment reminder and motivator. It will contain the date and the time of appointment, the location, and the name of the treating physician (Figure 3). To comply with medical confidentiality, the message will not contain any information on the health status of the child. Each text message sent will include about 300 characters including spaces. The method ‘message received’ will be used to ensure that the message was actually sent. For calls, a medical administrative assistant will phone 48 hours before the scheduled appointment, between 08:00 and 12:00 AM with communication in French or in English. A maximum of three calls attempts will be made. During the phone call, the medical secretary will remind the participant of the date and the location of his/her appointment and of the name of the treating physician. The name of the participant or the child will not be mentioned. In both SMSs and phone calls, communication is unidirectional towards the participant who cannot in return contact the medical secretary. This phone call procedure will be identical for the group receiving only phone calls (Group 3). Concerning the group receiving only the SMS (Group 2), the same procedure for sending SMS will be followed, and the SMS will be sent 48 hours before the appointment instead of 72 hours. It is important to note that, the content of communication (by SMS or by voice call) will be the same for all interventions.

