### Outcome measures

#### Primary outcomes

Table 1 shows an overview of the outcomes and statistical method that will be used. The primary outcome will be the presence at appointment. It will be measured by effectiveness, and efficiency related to both financial cost and working time. Effectiveness will be the capability of producing a presence at an appointment (attendance). We will measure three aspects of efficiency using the following ratios: i) presence at appointment/financial cost x working time; ii) presence at appointment/financial cost; and iii) presence at appointment/working time. Time for text message intervention will be measured from the start of writing the message until the sending. For phone calls, this time measure will begin when we make the first call (not when the participant picks up the phone) and will stop at the end of the communication. The cost of each call and SMS will be evaluated using a prepaid plan. The prepaid plan means that the phone will have a financial amount of communication known before the call. After call, the difference will be made with the remaining amounts. Each SMS will cost 50 or 100 Francs of Financial Community of Africa (FCFA) (approximately 0.076 € or 0.152 €).

**Table 1 T1:** Overview of outcome measures

**Outcomes measures**	**Scale**	**Type**	**Measure**	**Analysis method**

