#### Secondary outcomes

The intervention will be considered unsuccessful if we do not receive ‘message received’ after sending of SMS, or if we call in vain after three attempts between 8:00 and 12:00 am. For those who will receive both SMS and phone call, the intervention will be considered unsuccessful if these two conditions are fulfilled.

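### As written, the call clock runs on between dialling attempts and has no stop when nobody answers, so working time in the call groups can be overstated by an amount the protocol does not let us fix

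*Protocol article*

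**What the plan says.** All references are to the protocol article.

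- **Call clock (Primary outcomes).** The start is explicit: "this time measure will begin when we make the first call (not when the participant picks up the phone"). So is the stop: the measure "will stop at the end of the communication".
- **Number of attempts (Reminder intervention).** "A maximum of three calls attempts will be made", and calls are placed "between 08:00 and 12:00 AM with communication in French or in English".
- **Failed calls (Secondary outcomes).** A call reminder is unsuccessful "if we call in vain after three attempts between 8:00 and 12:00 am".
- **SMS clock (Primary outcomes).** "Time for text message intervention will be measured from the start of writing the message until the sending".
- **Use of the measure.** The three efficiency ratios are "i) presence at appointment/financial cost x working time; ii) presence at appointment/financial cost; and iii) presence at appointment/working time". Table 1 lists working time and efficiency among the primary outcomes and compares their means by t-test. The Abstract hypothesises that SMS alone will prove the most efficient.

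The article does not give the spacing of attempts, the expected share of calls answered, or what the assistant does between attempts.

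**The concern.** The rule fixes two clock times, the first attempt and the end of the conversation, and counts everything between them. That is sound when the first call is answered, since dialling and ringing are genuine work. When a later attempt succeeds, the recorded time also contains the interval since the first attempt. The SMS clock covers hands-on time only, so the two channels would be timed on different bases.

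The error has one direction. It can add to call time in Groups 3 and 4 but cannot add to SMS time, so it leans towards the result the trial expects on efficiency. Working time is in the primary tier and enters ratios (i) and (iii), taking ratio (i) as attendance divided by the product of cost and time. A few long gaps could also widen the spread that the t-test has to work with.

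The same sentence leaves a second gap. After three unanswered attempts there is no conversation to end, so the working time of an unreached participant is undefined, although the Analysis plan keeps that participant under intention to treat.

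**Working it through.** **Plan's own figures.** The article gives no figure for call time to reproduce. Its sample size (50 per group; 50/0.9 = 55.6, so 56; 4 × 56 = 224) does reproduce, but it rests on attendance and is not at issue.

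**Inputs from the article.** At most three attempts, hence at most two gaps per participant. The window is 08:00 to 12:00, read here as noon, so 240 minutes bounds the recorded time for attempts within one morning.

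**Assumed inputs (not in the article).** An answered call takes 2 min and an unanswered attempt 0.5 min. The shares reached on attempts 1, 2 and 3 (a1, a2, a3) range from 80/10/5% to 50/25/15%. The gap between attempts is g minutes.

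**Formulas, among participants reached**

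- Hands-on mean: h = (2·a1 + 2.5·a2 + 3·a3) / (a1 + a2 + a3)
- Mean number of gaps: m = (a2 + 2·a3) / (a1 + a2 + a3)
- Recorded mean under the literal rule: h + m·g
- Inflation: (h + m·g) / h

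**Numbers**

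- 80/10/5%: h = (1.60 + 0.25 + 0.15)/0.95 = 2.11 min; m = 0.20/0.95 = 0.211.
- 50/25/15%: h = (1.00 + 0.625 + 0.45)/0.90 = 2.31 min; m = 0.55/0.90 = 0.611.

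| Gap g (min) | Recorded mean, 80/10/5% | Inflation | Recorded mean, 50/25/15% | Inflation |
|---|---|---|---|---|
| 0 | 2.1 | 1.0 | 2.3 | 1.0 |
| 1 | 2.3 | 1.1 | 2.9 | 1.3 |
| 5 | 3.2 | 1.5 | 5.4 | 2.3 |
| 15 | 5.3 | 2.5 | 11.5 | 5.0 |
| 60 | 14.7 | 7.0 | 39.0 | 16.9 |

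**Second set of assumptions.** Take 1.5 min for an answered call, 0.5 min for an unanswered one, and a constant answer probability q per attempt. For q = 0.9, 0.7 and 0.5 the inflation is 1.07, 1.2 and 1.3 at a 1-minute gap; 1.7, 3.1 and 4.2 at 10 minutes; and 5.2, 13.4 and 20.2 at 60 minutes. If every first call is answered, it is 1.0 at any gap.

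**What this does to ratio (iii).** The factors above apply to mean call time. If the ratio is formed per participant and then averaged, as the mean of efficiency in Table 1 suggests, the effect is smaller, because only late-reached participants lose value. Among those reached, with attendance unrelated to the attempt number, the mean of 1/time at g = 60 changes as follows:

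- 80/10/5%: from (0.8/2 + 0.1/2.5 + 0.05/3)/0.95 = 0.481 to (0.8/2 + 0.1/62.5 + 0.05/123)/0.95 = 0.423, a fall of 12%.
- 50/25/15%: from (0.5/2 + 0.25/2.5 + 0.15/3)/0.90 = 0.444 to (0.5/2 + 0.25/62.5 + 0.15/123)/0.90 = 0.284, a fall of 36%.

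In Group 4 the call is only part of the working time, so the inflation of the total is lower than the table shows.

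**The case against.** The strongest reply is that the rule's contrast is with the moment of pick-up. The authors may have wanted only to include dialling and ringing, without thinking about redials. On that view the sentence is ambiguous for repeat attempts rather than an instruction to count waiting time. This partly stands: the intention is unclear. But the start is tied to the first call in a protocol that allows three, and nothing pauses the clock, so an assistant following the text would record the gap. If it is only ambiguous, staff or sites could still time redials differently.

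A reader might infer that idle time will certainly be counted and that calls will look far less time-efficient than they are. The documents do not support that. They give no spacing or answer rates and do not say what the assistant does between attempts; time spent waiting solely to redial one participant could fairly be charged to that participant. Prompt redialling makes the effect close to nil.

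A reader might also infer that SMS would win only because of the clock. That is not shown either. The SMS is typed by hand at about 300 characters, its writing is timed, and no SMS time is available to show a changed ranking. Leaving the delivery-receipt check out of SMS time is a minor point.

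Three further objections were weighed:

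- The Sample size section names attendance as the primary objective. That limits the severity, though Table 1 still places working time in the primary tier.
- Attempt spacing is detail an article may leave to the full protocol. That is fair for the spacing, but the start and stop rule is stated here and is itself the problem.
- Times already recorded may not be recoverable. This stands and limits the fix.

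**Conclusion.** The concern holds as a defect in the written timing rule. For participants reached on attempt 2 or 3, the literal rule counts the gaps between attempts as working time, and for unreached participants it defines no time at all. The first of these can only lengthen call time, against Groups 3 and 4. It reaches the working-time comparison and ratios (i) and (iii). Attendance, financial cost and ratio (ii) are not affected.

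The size cannot be settled from the documents. There is no inflation with immediate redialling or answered first calls. It is about 1.1 to 1.3 times at a 1-minute gap, and several-fold to more than tenfold at gaps of 15 to 60 minutes, all for mean call time under assumed call lengths and answer rates. The effect on an averaged per-participant ratio is smaller. No reversal of the ranking between SMS and calls is claimed.

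Severity: should be fixed.

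**What to change.** Redefine call working time as the sum, over every attempt including unanswered ones, of the time from dialling to hanging up, leaving out the intervals between attempts. This also gives unreached participants a defined value. Time the SMS on the same hands-on basis: writing, sending and any check of the delivery receipt.

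Recruitment is described as ongoing (Trial status), so apply the rule to all calls still to be made. For pairs already timed, rebuild the call time only where a call log exists; the article does not say that logs were kept.

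The cost is a short change to the outcome definition and one extra log line per attempt. Earlier pairs without a log remain on the old basis and should be reported as such, ideally with the working-time comparison shown with and without them.

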**Primary**				
Presence at appointment				
• Efficacy	Nominal	Binary	% present at appointment	Chi-square test
				Additive and multiplicative scales for synergy measurement
• Efficiency	Ratio	Continuous	Mean of efficiency	*T*-test
- Working time	Ratio	Continuous	Mean of working time	*T*-test
- Financial cost	Ratio	Continuous	Mean of financial cost	*T*-test

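### The efficiency measure has no defined time, and possibly a zero cost, for call participants who are never reached, so they can drop out of the call v SMS comparison

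*Protocol article*

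**What the plan says.** All references are to the protocol article.

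- **Call time** (Primary outcomes): the clock starts at the first attempt, not at pick-up, and "will stop at the end of the communication".
- **Call cost** (Primary outcomes): the drop in the prepaid balance. "After call, the difference will be made with the remaining amounts".
- **SMS time and cost** (Primary outcomes): "Time for text message intervention will be measured from the start of writing the message until the sending". Each SMS costs 50 or 100 FCFA.
- **Ratios** (Primary outcomes): presence over the product of cost and time, and also "ii) presence at appointment/financial cost; and iii) presence at appointment/working time".
- **Summary and test** (Table 1, primary tier): "Mean of efficiency", treated as continuous and compared by t-test. Working time and cost are handled in the same way.
- **Failed calls**: the Reminder intervention section allows at most three attempts. The Secondary outcomes section counts an intervention as unsuccessful "if we call in vain after three attempts between 8:00 and 12:00 am".
- **Analysis set**: the Sample size section excludes participants with incomplete data. That section and the Analysis plan both state intention to treat.

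**The concern.** The rules for time and cost assume that a call is answered. A Group 3 (call only) participant who is never reached has a start time and no stop time, so presence/time has no denominator. If unanswered calls are not charged, the balance difference is zero and both ratios that contain cost divide by zero, whether or not the child attends. Under the incomplete-data rule such a participant can leave the efficiency and working-time comparisons.

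A failed SMS in Group 2 behaves differently. Its time ends at sending and its cost is 50 or 100 FCFA, so all three ratios exist whether or not it is delivered. The comparison of call with SMS could then set reached call participants against all SMS participants. Being reached is a post-randomisation event and plausibly related to attendance, so the comparison would no longer follow intention to treat.

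Efficiency is half of the trial's objective and sits in the primary tier of Table 1. The Abstract also states a hypothesis about it, that SMS alone is the most efficient.

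**Working it through.** **The plan's own figures.** The article gives no figure for efficiency, no rate of unreached calls and no call duration. Its group size reproduces: 50/(1 - 0.10) = 55.6, so 56 per group and 224 in total. With 10%, 20% or 30% unreached (assumed), 5.6, 11.2 or 16.8 of 56, about 6, 11 or 17 participants in Group 3, would lack a time ratio.

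**Inputs.** From the Sample size section: attendance with calls, p = 0.596. Assumed: share unreached u = 0.20; attendance among the unreached a = 0.45; time per answered call t_r = 2 min; time per failed series t_u = 3 min.

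**Presence/time with the plan's estimator (mean of individual ratios)**

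1. Attendance among the reached: (p - u·a)/(1 - u) = (0.596 - 0.090)/0.80 = 0.6325.
2. Mean over reached participants only: 0.6325/2 = 0.316 per minute.
3. Mean over all randomised: 0.80 × 0.31625 + 0.20 × 0.45/3 = 0.253 + 0.030 = 0.283 per minute.
4. Overstatement: 0.31625/0.283 = 1.117, about +12%.

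**Dependence on the length of a failed series**, other inputs unchanged:

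| t_u (min) | Mean, all randomised | Reached only v all |
|---|---|---|
| 1 | 0.253 + 0.0900 = 0.3430 | -7.8% |
| 1.5 | 0.253 + 0.0600 = 0.3130 | +1.0% |
| 2 | 0.253 + 0.0450 = 0.2980 | +6.1% |
| 3 | 0.253 + 0.0300 = 0.2830 | +11.7% |
| 60 | 0.253 + 0.0015 = 0.2545 | +24.3% |

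The sign changes where a/t_u equals the reached-only ratio: t_u = 2 × 0.45/0.6325 = 1.42 min. With a = 0.50, attendance among the reached is (0.596 - 0.100)/0.80 = 0.62 and the change comes at 2 × 0.50/0.62 = 1.61 min.

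**Range.** With times held at 2 and 3 min, u from 10% to 30% and a from 30% to 59.6% give about +3% to +28%. If t_u also varies from 1 to 240 min, with a from 40% to 59.6%, the range at u = 30% is -23.1% to +42.6%.

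**Mean working time.** Reached only: 2 min. All randomised: 0.80 × 2 + 0.20 × 3 = 2.2 min. Dropping the unreached understates it by 9% (2/2.2 = 0.909).

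**Presence/cost, if unanswered calls are free.** A mean of individual ratios does not exist for the full group, so the comparator must be an arm-level ratio. With cost c per answered call, reached only gives 0.6325/c, and all randomised gives 0.596/(0.80c) = 0.745/c. The ratio is 0.849, or -15%: attended visits that used no credit are lost. In general the ratio is 1 - u·a/p, which runs from -5% (u = 0.10, a = 0.30) to -30% (u = 0.30, a = 0.596).

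**The case against.** The strongest reply is that this is a gap in data-collection detail, which a journal article may leave to the full protocol. Starting the clock before pick-up suggests that unanswered dialling counts as work, so staff would naturally stop it at the last failed attempt. The intention-to-treat statement also points towards keeping these participants. No section says that they are dropped.

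Much of this stands. Exclusion is what follows from reading the stop rule and the incomplete-data rule literally; it is not a stated intention. Two things remain. The article does not leave the matter open: it fixes the start, stop, cost, ratios, summary and test, and those rules fail for a case that it foresees. And a sensible stop time would not help the cost ratios, because a per-person ratio with a zero denominator cannot be repaired by recording more detail.

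A reader might infer more than this, and the documents do not support it:

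- **That calls must come out looking too efficient.** The sign depends on how long failed attempts take, which the article does not give, and presence/cost moves the opposite way.
- **That the +12% should be larger.** Setting the reached-only mean against a ratio of totals, 0.596/(0.80 × 2 + 0.20 × 3) = 0.271, gives +17%, but part of that comes from changing the estimator.
- **That Group 4 is affected in the same way.** Its participants also receive an SMS, so their cost is never zero and their SMS time is recorded. Only the call component is undefined.

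**Conclusion.** The point holds as a defect in how a primary-tier measure is defined. For unreached Group 3 participants the call time has no end and the cost denominator may be zero. Taken with the exclusion of incomplete data, this permits a post-randomisation exclusion that conflicts with intention to treat and that Group 2 does not share.

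The direction is not established. Reached-only analysis does not understate presence/time when a failed series takes at least as long as an answered call and the unreached attend no more often than the reached. That is plausible, since the clock starts at the first of up to three attempts within the 08:00 to 12:00 window. It understates presence/time when failed attempts are clearly shorter, below about 1.4 to 1.6 min in the cases worked. The figure of about +12% rests wholly on assumed values for the unreached share, their attendance and both durations. The presence/cost result rests further on unanswered calls being free. The attendance comparison and the sample size are not affected.

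**What to change.** 1. State that for an unanswered call the working time ends at the end of the last attempt, and say whether waiting between attempts counts. The second part also matters for participants reached on a later attempt.
2. Record the credit actually used as the cost, zero included.
3. Keep everyone randomised to Groups 2 to 4 in the efficiency, time and cost comparisons.
4. Compute efficiency per arm as total attendance over total cost and over total time, so that a zero never stands in an individual denominator. For the ratio with the product of cost and time, use arm means; dividing a total by a product of two totals makes the result depend on the number of participants.
5. Compare arms with a bootstrap confidence interval that resamples adult-child pairs within arm, in place of the t-test on individual ratios.

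The cost is recording the end time of failed attempts, which the article does not say is done now, and a little more analysis work. The Trial status section describes recruitment as ongoing, so the recording rule should be settled first, because end times that were not noted may not be recoverable.

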**Primary**				
Presence at appointment				
• Efficacy	Nominal	Binary	% present at appointment	Chi-square test
				Additive and multiplicative scales for synergy measurement
• Efficiency	Ratio	Continuous	Mean of efficiency	*T*-test
- Working time	Ratio	Continuous	Mean of working time	*T*-test
- Financial cost	Ratio	Continuous	Mean of financial cost	*T*-test
**Secondary**				
Success of intervention	Nominal	Binary	% success of intervention	Chi-square test

#### Secondary outcomes

The intervention will be considered unsuccessful if we do not receive ‘message received’ after sending of SMS, or if we call in vain after three attempts between 8:00 and 12:00 am. For those who will receive both SMS and phone call, the intervention will be considered unsuccessful if these two conditions are fulfilled.

#### Sample size

The primary objective is to measure the patient presence at their scheduled appointment. The calculation of the sample size will be based on the comparison of proportions of presence at appointment. The value of alpha is 0.05. The test is two-tailed. We assume that the presence at appointments using SMS as reminder and phone calls is, respectively, 59.0% and 59.6% [11]. We also assume that the difference would be 25% between the group that will receive both SMS and phone calls and the groups that will receive only an SMS or only phone calls. The minimum size of the sample required will be 50 subjects in each group for analysis by intention to treat with 80% power and a significance level of 0.05. We will exclude from analysis the participants with incomplete data. For this we assume a 10% attrition rate. Thus, we will need 224 subjects (56 in each group). WinPepi has been used to calculate the size of the sample [20].

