**Methods/Design:**

We will carry out a multicenter single-blind, randomized, factorial controlled trial. A randomization list will be electronically generated using random block sizes. Central allocation will be determined by sequentially numbered. A total of 224 subjects will be randomized into four groups (SMS, Call, SMS + Call, and Control) with an allocation ratio of 1:1:1:1. SMS and calls will be sent between 48 and 72 hours before the scheduled appointment. A medical assistant will send out text messages and will call participants. Our primary outcome is appointment measured by efficacy and efficiency of interventions. We hypothesize that two reminders (concomitant use of SMS and phone calls) as an appointment reminder is more effective to improve appointment compared to one reminder (only SMS or only call), and that the most efficient is use of only SMS. The analysis will be intention to treat.

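### The plan promises intention to treat but excludes participants with incomplete data, and does not confine the exclusion to the outcome whose data are missing

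*Protocol article*

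**What the plan says.** The Abstract states "The analysis will be intention to treat", and the Analysis plan section repeats the principle. Sample size ties the calculation to the same principle: "The minimum size of the sample required will be 50 subjects in each group for analysis by intention to treat with 80% power". The sentence after that reads "We will exclude from analysis the participants with incomplete data". A 10% attrition allowance follows, which gives 56 per group and 224 in all.

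Other sections bear on what could be incomplete:

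- **Blinding:** a nurse acting as outcome assessor records whether the patient was present or absent. No difference by group is described.
- **Primary outcomes:** working time and cost are measured for each SMS and call, and both enter the efficiency ratios.
- **Control:** Group 1 gets no reminder, so it generates no reminder time or cost.
- **Secondary outcomes:** an SMS without a delivery receipt, or three unanswered call attempts, is classed as an unsuccessful intervention. In the group given both reminders, both must fail.

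**The concern.** The two rules cannot both govern the attendance analysis. Under intention to treat, every randomised pair is analysed in its assigned group. The exclusion sentence removes some of them, without defining incomplete and without saying which analysis it applies to. It stands in a paragraph about sizing the trial on presence at the appointment, so it reads naturally as applying to the primary outcome.

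The rule fits this outcome poorly. Someone who does not come has an observed result, absence, so attendance itself should seldom be missing. A pair could then be dropped for a gap in another field although its attendance is known. If the dropped pairs differ from the rest in attendance, and are dropped more from one group than another, the comparison is biased. Leaving both rules in place also means that the primary population could be chosen after the data are seen.

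**Working it through.** **1. The plan's own figures.** Inputs from Sample size: two-sided alpha 0.05, power 80%, attendance 59.0% (SMS) or 59.6% (call), and 25 points more with both reminders. With the pooled-variance formula and no continuity correction,

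n = [1.960·√(2·p̄(1−p̄)) + 0.842·√(p₁(1−p₁) + p₂(1−p₂))]² / (p₂−p₁)²

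- For 59.0% v 84.0%, p̄ = 0.715. The numerator is (1.960·√0.4076 + 0.842·√0.3763)² = 3.124, and 3.124 / 0.0625 = 49.99, so 50.
- For 59.6% v 84.6%, the same formula gives 49.3, so 50.
- Inflation: 50 / 0.9 = 55.6, so 56 per group, and 4 × 56 = 224.

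All three stated figures reproduce. The trial is therefore sized on the expectation that about 6 of 56 pairs per group will be left out. The exclusion is a planned step.

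**2. What keeping everyone does to power.** Exact power of the uncorrected chi-square test for 59% v 84%, by enumerating the two binomials, is 80.8% with 50 per group and 85.1% with 56.

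**3. How much an observed difference could move, with no assumption about why data are missing.** Suppose 6 are excluded from each of two groups of 56, and the remaining 50 show 84% v 59% (42 v 29.5 attenders).

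- Lowest all-randomised difference: 42/56 − (29.5 + 6)/56 = 75.0% − 63.4% = 11.6 points.
- Highest: (42 + 6)/56 − 29.5/56 = 85.7% − 52.7% = 33.0 points.

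These are extreme bounds, not expected values.

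**4. Illustration of arm-dependent exclusion.** The assumptions, none of them in the article, are: no true effect, attendance 59% in both groups (the plan's SMS figure, borrowed), a fraction f = 10% excluded from one group and none from the other, and attendance q among those excluded. The observed rate in the affected group is (0.59 − f·q)/(1 − f).

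| q | Observed rate | Apparent gain |
|---|---|---|
| 0% | 0.590/0.9 = 65.6% | 6.6 points |
| 20% | 0.570/0.9 = 63.3% | 4.3 points |
| 40% | 0.550/0.9 = 61.1% | 2.1 points |
| 59% | 0.531/0.9 = 59.0% | none |

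With 56 randomised per group, the two-sided type I error is about 11%, 7% and 6% in the first three rows. If both groups lose 10% in the same way, both show the same rate under no effect, and the type I error is about 5% even when only non-attenders are dropped.

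**The case against.** The strongest reply is that nothing in the article makes incompleteness depend on the arm.

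- The 10% allowance is applied to every group, including control, which has no reminder data. That fits ordinary attrition better than gaps in time or cost.
- Participants who could not be reached are not called incomplete. Secondary outcomes records them as unsuccessful, and that percentage can be computed only if they stay in the data.
- For calls, "this time measure will begin when we make the first call (not when the participant picks up the phone", so dialling time counts. Cost comes from the change in prepaid balance and can be computed whether or not anyone answers. SMS timing ends at sending, so an undelivered SMS still has a time.
- An attendance record can be lost in any group, and participant data are collected before assignment.
- In Group 4 v Group 3, one of the two comparisons used for sizing, both groups receive calls, so a bias from unanswered calls would largely cancel.
- A condensed article may leave the definition of incomplete to the full protocol or analysis plan.

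Most of this stands. A reader might infer that the rule removes unreached participants from the call groups only, and hence that randomisation is already compromised. The documents do not support that: it would require reminder-process gaps to count as incomplete, and no section says they do. The end of timing for a call nobody answers is unclear, which leaves that route open but does not establish it.

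The last reply does not remove the point. The article does more than omit a definition: it states an unqualified exclusion from analysis directly after a sample size described as being for intention to treat.

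**Conclusion.** The conflict is real and rests on the text alone: a stated principle, a stated rule against it, and a sample size built to absorb the rule. Applied as written, the rule can drop randomised pairs whose attendance is known, about 6 per group on the plan's own allowance.

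Bias from arm-dependent exclusion is a conditional risk. It needs exclusion that differs by group and is related to attendance. Under the assumed one-sided 10% exclusion it is 2.1 to 6.6 points when 0% to 40% of those excluded attended. It vanishes if they attended like everyone else, and is small if exclusion is equal and unrelated to arm. Exclusion fractions above the plan's 10% have no basis in the article and are not relied on here. The sample-size arithmetic is sound.

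**What to change.** Replace the exclusion sentence with wording to this effect:

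- Attendance is analysed in all 224 randomised pairs, in the group assigned.
- A participant who does not come to the scheduled appointment is counted as absent.
- A truly missing attendance record is counted as absent in the primary analysis, with a sensitivity analysis that treats such records differently.
- Missing time or cost data affect only the efficiency analyses.

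Reword the 10% attrition sentence to match, since it now refers to the exclusion. The total of 224 need not change: with all 56 per group kept, exact power for 59% v 84% is about 85% instead of about 81% with 50.

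The cost is a few sentences, with no more participants and no new data. The one downside is small: counting a lost record as absent may slightly understate attendance, which the sensitivity analysis would show.
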